### Study endpoints

The primary endpoint will be the proportion of the population with specific antibodies against SARS-CoV-2.

Secondary endpoints will be as follows:The proportion of the population with specific antibodies against SARS-CoV-2 in each subgroup of age (60 and over, 19–59 years old, teenagers aged 15–18 and those aged 10–14 years) and by gender (males, females).The proportion of asymptomatic infections (presence of antibodies in patients with no clinical signs of SARS-CoV-2 infection) in the population, in each subgroup of age (60 and over, 19–59 years old, teenagers aged 15–18 and those aged 10–14 years) and by gender (males, females).

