### Sample size calculation

Using the sample size calculator available on Openepi [31] (http://www.openepi.com/SampleSize/SSPropor.htm), with an expected SARS-CoV-2 seroprevalence of 10%, an accuracy of ± 3%, an alpha risk = 5% and no design effect (Deff = 1), we need at least 384 persons in each gender and age stratum at the final round (fourth timepoint). This number has been rounded to 452 to account for approximately 85% usable data.

Therefore, considering a non-response rate of 70% at inclusion and 30% between the data collection rounds (one to four), Table 1 (below) gives the number of subjects required per age and gender group per visit. At the final round (fourth timepoint), there should be 452 for each stratum. The details of the sample size calculation are presented in Table 2.

**Table 1 Tab1:** Distribution of the city zones for the socio-anthropological study

	Bobo Dioulasso	Ouagadougou
Residential/central	1	1
Residential /peripheral	1	1
Poorer/central	1	1
Poorer/ peripheral	1	1
Total	4	4

**Table 2 Tab2:** The study sample calculation strategy

Age and gender groups	Average number of people per household	Average number of households per EA* in the study cities	Number of EA needed for the study	Estimated number of people in the selected EA	Estimated number of people to contact	Estimated number of people to select in each EA	Estimated number of people needed after round 1	Estimated number of people needed after round 2	Estimated number of people needed after round 3	Estimated number of people needed after round 4
Men and women aged 60 and over	0.15	220	160	5280	4393	28	1318	922	646	452
Men aged 19 to 59	1.26	220	160	44,352	4393	28	1318	922	646	452
Women aged 19 to 59	1.10	220	160	38,720	4393	28	1318	922	646	452
Teenagers aged 15 to 18	0.51	220	160	17,952	2152	14	0	0	646	452
Teenagers aged 10 to 14	0.61	220	160	21,472	2152	14	0	0	646	452
Total				127,776	17,483	112	3953	2767	3229	2260

*EA** Enumeration Area

To avoid the design effect (Deff = 1) in the calculation of the sample size, the sampling method will be two-stage random sampling with a probability proportional to their size in the resident population according to the data from the National Institute of Statistics and Demography survey (INSD).

To contact the 17,483 people for inclusion we will randomly choose 160 Enumeration Areas (EA) in Ouagadougou and Bobo-Dioulasso. In the two cities together 160 EA out of 1728 will be selected with a probability proportional to their size.

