After selection of the EAs, the selection of individuals (second degree), will be done as follows:Complete a census and numbering of all concessions (can include several households), all households and target persons (men and women aged 60 and over, women aged 19–59, men aged 19–59, teenagers aged 15–18 and children aged 10–14 years),Number (from 1 to n) all the targeted residents by category,From each category, 28 residents will then be selected among adults and 14 teenagers from every EA.

If a selected participant is unavailable or refuses to participate in the study, he/she will be replaced with an individual randomly chosen from the same age and gender group in the same EA and in the same city. If the number of participants to select cannot be reached in an EA, it will be completed with the subsequent individuals in the randomization list. This strategy allows implicit stratification and is easy to perform. It simply requires that the sampling frame be sorted geographically before sampling systematically, with a probability to be selected proportional to the size. It also automatically provides a sample that is proportionally distributed among geographic subdivisions in the study area. Furthermore, it will make it easier to find the respondents in the field, since the interviewers will already be in touch with them through the census. Sample collection of teenagers will start at round three, enabling field investigators to obtain parental consent for their children to participate in the study during the first two rounds of data collection.

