### Statistical analysis

For the statistical analysis, this research project will adopt a dynamic approach and will constantly integrate latest knowledge emerging about COVID-19. A first analysis will be performed after the first collection on day 0, to enable important information that could be useful for the fight against COVID-19 to be relayed to the authorities in Burkina Faso.

The following analyses will be performed [7]:Calculation of the cumulative incidence by age group: i.e., the proportion of individuals who are seropositive for SARS-CoV-2 infection according to age (60 and over, 19–59 years old, teenagers aged 15–18 and children aged 10–14 years).Calculation of the cumulative incidence by gender: i.e., the proportion of individuals who are seropositive for SARS-CoV-2 infection according to gender (men, women).Serological response to infection (if the serological tests enable us to evaluate this criterion): i.e., the course of serum levels of specific antibodies against SARS-CoV-2 (increase in titers across the different measurement timepoints).Describe and compare individual, socio-economic characteristics, presence of comorbidities and exposure according to serological status of the population.

Quantitative variables will be described as mean ± standard deviation (SD) and median (range) and compared using the Student t or Mann–Whitney U tests as appropriate. Qualitative variables will be described as number and percentage and compared using the chi square or Fisher’s exact test, as appropriate.

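### Gender-specific seroprevalence, and the overall figure if computed the same way, describes an artificial age mix, because near-equal numbers are sampled from very unequal age groups and no weighting is stated

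*Protocol article*

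**What the plan says.** All references are to the Protocol article, Phase 1.

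- **Target.** Study endpoints: "The primary endpoint will be the proportion of the population with specific antibodies against SARS-CoV-2". Inclusion criteria set the lower age limit at 10 years. Estimates by age group and by gender are secondary endpoints.
- **Sampling.** Sample size calculation: "From each category, 28 residents will then be selected among adults and 14 teenagers from every EA". Table 2 plans 452 people at round 4 in each of five groups: 60 and over, men 19 to 59, women 19 to 59, 15 to 18, and 10 to 14.
- **Timing.** Same section: "Sample collection of teenagers will start at round three". Table 2 prints 0 for both younger groups after rounds 1 and 2.
- **Estimator.** Statistical analysis defines cumulative incidence by gender as "the proportion of individuals who are seropositive for SARS-CoV-2 infection according to gender (men, women". Qualitative variables are "compared using the chi square or Fisher’s exact test, as appropriate". No formula is given for the overall proportion.
- **Early release.** Statistical analysis plans a first analysis after day 0, to be passed to the national authorities.
- **Balance claimed.** The sampling text claims proportionality only across geographic subdivisions, not across age groups.

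**The concern.** Selecting enumeration areas (EAs) with probability proportional to size and then taking a fixed number per category roughly equalises selection chances within a category. It does not do so across categories. A category with few people is sampled far more heavily than one with many, and a simple proportion pooled over categories inherits that imbalance.

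The gender estimate pools over age by construction, and so does the overall one. If infection differs by age, which the plan allows for by stratifying and reporting on age, neither simple proportion estimates the stated population quantity. At stake are the secondary gender estimates directly, the primary endpoint if it is calculated in the same manner, and the day-0 result sent to policy-makers, which contains nobody aged 10 to 18.

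**Working it through.** **1. The plan's own figures reproduce.** Inputs: "with an expected SARS-CoV-2 seroprevalence of 10%, an accuracy of ± 3%, an alpha risk = 5% and no design effect (Deff = 1".

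- n = 1.96² × 0.10 × 0.90 / 0.03² = 384, matching "we need at least 384 persons in each gender and age stratum at the final round (fourth timepoint".
- 384 / 0.85 = 451.8, matching "This number has been rounded to 452 to account for approximately 85% usable data".
- Dividing by 0.7 per round gives 645.7, 922.4 and 1,317.8. Dividing by 0.3 at inclusion gives 4,392.6 for adult groups and 645.7 / 0.3 = 2,152.4 for younger groups. These are the Table 2 entries.

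The sizing is therefore for precision within each group. It is the pooling across groups that needs checking.

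**2. Population and sample shares.** Population counts are Table 2's estimated people in the selected EAs (total 127,776). Sample shares come from its per-round columns.

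| Group | People | Population share | Rounds 1–2 | Rounds 3–4 |
|---|---|---|---|---|
| 60 and over | 5,280 | 4.1% | 33.3% | 20% |
| Men 19–59 | 44,352 | 34.7% | 33.3% | 20% |
| Women 19–59 | 38,720 | 30.3% | 33.3% | 20% |
| 15–18 | 17,952 | 14.0% | 0% | 20% |
| 10–14 | 21,472 | 16.8% | 0% | 20% |

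The planned contact fraction is 4,393 / 5,280 = 83% for people aged 60 and over and 4,393 / 44,352 = 9.9% for men aged 19 to 59, a ratio of 8.4.

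**3. Bias among adults, rounds 1–2.** People aged 60 and over are 5,280 / 88,352 = 5.98% of adults in the population and 33.33% of the sample. So

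simple − true = (0.3333 − 0.0598) × (p60+ − p19–59) = 0.2736 × gap.

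**4. Bias for ages 10 and over, rounds 3–4.** Sample weights are 20 / 40 / 40% for 60+ / 19–59 / 10–18. Population weights are 4.13 / 65.01 / 30.85%.

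The rates below are assumptions, since the documents give none by age.

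| Assumed rates (60+ / 19–59 / 10–18) | Adults: true, simple, bias | 10+: true, simple, bias |
|---|---|---|
| Equal in all groups | bias 0 | bias 0 |
| 8 / 10 / 10% | 9.88, 9.33, −0.55 | 9.92, 9.60, −0.32 |
| 5 / 15 / 10% | 14.40, 11.67, −2.74 | 13.04, 11.00, −2.04 |
| 20 / 10 / 5% | 10.60, 13.33, +2.74 | 8.87, 10.00, +1.13 |

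**5. Gender, rounds 1–2.** Table 2 does not split the 60-and-over group by gender, so assume half are women. In the sample, 659 / (659 + 1,318) = 33.3% of women are 60 or over. In the population it is 2,640 / (2,640 + 38,720) = 6.4%. The multiplier is 0.3333 − 0.0638 = 0.2695, giving a bias of 0.54 points for a 2-point gap and 2.7 points for a 10-point gap. For men the population share is 2,640 / 46,992 = 5.6% and the results are nearly the same.

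**6. Scale.** At 10% prevalence the simple 95% half-width of the overall figure is 1.96 × √(0.09 / 3,953) = 0.9 points at round 1 and 1.96 × √(0.09 / 2,260) = 1.2 points at round 4. The larger assumed age gaps give a bias beyond this; the mild one does not.

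**7. Cost of weighting.** Kish factor = Σ (population share² / sample share). Adults: 3 × (0.0598² + 0.5020² + 0.4382²) = 1.34. Five groups: 5 × (0.0413² + 0.3471² + 0.3030² + 0.1405² + 0.1680²) = 1.31. Interval widths grow by √1.34 = 1.16 and √1.31 = 1.14.

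**The case against.** **The article does not say unweighted.** The gender definition explains a term, and a weighted estimate is also a proportion. Weights are commonly left to a full protocol or analysis plan that is not shown, so their absence alone would be no finding. This has force. What remains is a mismatch: the article fixes strongly disproportionate sampling, defines the gender estimate plainly as a proportion of individuals, names ordinary chi-square and Fisher tests, and discusses balance only geographically. Followed as written, it yields the biased figure.

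**The primary endpoint.** A reader might infer that the plan defines the overall primary estimate as a raw proportion. It does not: only the target is named. The simple-proportion reading is explicit for gender and inferred for the overall figure.

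**A false trend.** Because the age mix changes between rounds 2 and 3, the simple figure can move without any change in infection, for example from 13.3% to 10.0% under 20 / 10 / 5%. A reader might infer that the plan would report such a trend. No comparison of seroprevalence between rounds is planned. The only analysis over time concerns antibody titers.

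**The late start below age 19 is disclosed**, with its reason, parental consent. That stands. The remaining request is to label the early results accordingly.

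**The larger biases rest on steep assumed age gradients**, in opposite directions. That also stands, so the mild and null cases are shown beside them.

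**Household invitation.** The participant section says all household members are invited, which does not fit a fixed take per category. Table 2 and the selection steps are treated here as the operative design.

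**Conclusion.** The concern holds in this form: the stated sampling and the stated gender estimator do not together deliver a population figure when seroprevalence differs by age, and the overall figure shares the problem if it is computed the same way. The sample shares are firm, as they come from Table 2. The size and direction of the bias are not, because they depend on unknown age-specific rates. Among adults in rounds 1 and 2 the bias is 0.27 times the gap between the 60-and-over and 19-to-59 rates: nil at equal rates, about 0.55 points for a 2-point gap and about 2.7 points for a 10-point gap. The gender figures also rest on the assumption that half of the 60-and-over group are women.

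Estimates by age group, for which the sample was sized, are little affected. Only the 19-to-59 group pools men and women 1:1 where the household means are 1.26 to 1.10. The documents support neither a claim that the primary endpoint is explicitly defined as a raw proportion nor a claim that a spurious trend will be reported.

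**What to change.** - Define the overall and gender-specific estimates as weighted by inverse selection probability, using the census of target persons planned in each selected EA, and/or post-stratified to the national statistics institute's age-by-gender structure. Use variances and gender comparisons that respect the weights and the sampling design.
- Label the day-0 and round-2 results as adults 19 and over. Give the estimate for the population aged 10 and over only from round 3.
- If rounds are compared at all, do so on the common age range of 19 and over, with the same weighting.

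The cost is revised analysis wording, a small amount of analysis work and overall intervals about 15% wider (Kish factor 1.31 to 1.34). No extra participants are needed to remove the bias. The inputs are not all shown to be in hand: Table 2 has no city breakdown and no gender split for the 60-and-over, 15-to-18 and 10-to-14 groups, so the gender split must come from the statistics institute or the EA census.

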### Data collection and management

Data collection in the general population will take place at four timepoints, each 21 ± 3 days apart. Blood samples will be drawn by trained and qualified personnel. In each household, the members of the household who accepted to participate will be invited to sign the informed consent form, and complete a questionnaire (Additional file 1) with socio-demographic data, comorbidities, symptoms related to SARS-CoV-2 infection and exposure, namely:Socio-demographic characteristics: age, profession, marital status, level of education, socio-professional category;Prior medical history:History of cardiovascular and thrombo-embolic disease: arterial hypertension, rhythm disturbances, cardiomyopathy, deep venous thrombosis, pulmonary embolism;History of metabolic diseases: diabetes mellitus, kidney failure;History of pulmonary disease: tuberculosis, asthma, chronic obstructive pulmonary disease (COPD);Other relevant medical history.Lifestyle habits: tobacco and alcohol consumption;Clinical signs of COVID-19: fever (temperature ≥ 38 °C), cough, dyspnea, etc.;Exposure to COVID-19: any contact with a confirmed case of COVID-19.

Persons who complete the questionnaire will be requested to give a blood sample to extract serum for the assessment of SARS-CoV-2 antibodies. Venous blood samples will be collected at the four different timepoints (Days 0, 21, 42, 63) to enable analysis in the laboratory. Blood will be collected by venous puncture performed by health workers within the participant’s home. In total, 4 ml of blood will be drawn in a 5 ml EDTA tube for each participant, at each timepoint.

The blood samples will be transported to the laboratory within 6 h of the collection, along with the relevant follow-up sheet for the blood samples. For transport to the laboratory, blood samples will be triple packed in an isotherm container containing an icebox to preserve the cold chain.

All blood samples will be analyzed in the Laboratory of the MURAZ center in Bobo-Dioulasso. Laboratory procedures involving handling of blood samples will be performed in a class 2 biosafety cabinet. For blood samples collected in the city of Bobo-Dioulasso, samples will be sent to the laboratory daily. Samples from Ouagadougou will also be sent daily to the laboratory of the national center for research and training on malaria in the same city where they will treated.

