### Implications

The results of this project will serve to shape public policy aimed at fighting the Covid-19 pandemic in Burkina Faso. The lessons learned from the management of the epidemic may serve as examples to the Burkinabe authorities to better design preventive strategies in the case of future epidemics or pandemics. To enable the dissemination and rapid use of the results of this study, we have already constituted a steering committee bringing together representatives from the Ministry for Health of Burkina Faso, experts in epidemiology, biology, politics, health systems and investigators for the current study. A non-medical organization that advocates for wider access to screening and treatment of COVID-19 (Réseau d’accès aux médicaments essentiels génériques) is also represented on the steering committee. The steering committee will meet every three months. During these meetings, the study investigators will provide an update on the advancement of the study procedures, and any difficulties encountered. The members of the committee will formulate recommendations for the implementation of the study, monitor study procedures, and provide advice about the interpretation of the findings that may be of use to decision-makers. The implication of political decision-makers, notably the Ministry for Health, in this study is a guarantee that the results will be rapidly translated into policy considerations to guide the strategy for response to the COVID-19 epidemic in Burkina Faso.

This research protocol can easily be adapted in any low-income country to generate accurate epidemiological, sociological, and anthropological data about the COVID-19 epidemic and adapt public health measure to control the disease. The lessons learned from the management of the epidemic may serve as examples to the Burkinabe authorities to better design preventive strategies in the case of future epidemics or pandemics.

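### Phase 1 compares seropositive and seronegative people with crude two-group tests, although the sample is fixed by age group in proportions far from the population, so age-linked factors can appear associated with serostatus (minor)

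*Protocol article*

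**What the plan says.** The Phase 1 Statistical analysis section lists, as its last item, "Describe and compare individual, socio-economic characteristics, presence of comorbidities and exposure according to serological status of the population". Quantitative variables are to be "compared using the Student t or Mann–Whitney U tests as appropriate" and qualitative variables "compared using the chi square or Fisher’s exact test, as appropriate". No model is named for Phase 1. The Phase 2 Statistical analysis section, by contrast, names logistic and Cox regression.

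The Phase 1 Data collection and management section gives the variables in question. They include "Socio-demographic characteristics: age, profession, marital status, level of education, socio-professional category", along with cardiovascular, metabolic and pulmonary history, tobacco and alcohol use, and contact with a confirmed case.

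Table 2 sets equal targets for three adult groups (60 and over, men 19 to 59, women 19 to 59) in every round. Ages 15 to 18 and 10 to 14 have zero participants in rounds 1 and 2, then 646 each in round 3 and 452 each in round 4.

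**The concern.** The sampling plan holds age group at fixed numbers, while the comparison by serostatus ignores age group. Profession, marital status, education, hypertension and diabetes can all be expected to vary with age. The plan also intends to estimate seroprevalence by age, so a difference by age is a live possibility. If there is one, a pooled crude test of an age-linked factor partly measures the age make-up of the seropositive and seronegative groups. It can reject when the factor has no relation to serostatus among people of the same age.

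The Implications section says "The results of this project will serve to shape public policy aimed at fighting the Covid-19 pandemic in Burkina Faso". A comorbidity or occupation reported as associated with infection could be read as a reason to target that group, when the difference reflects age and the quota for people aged 60 and over.

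**Working it through.** **How far the sample departs from the population (Table 2).**
- Adults in the selected areas: 5,280 + 44,352 + 38,720 = 88,352. Share aged 60 and over: 5,280 / 88,352 = 6.0%. The per-household averages agree: 0.15 / (0.15 + 1.26 + 1.10) = 6.0%.
- Round 1: 1,318 / 3,953 = 33.3% aged 60 and over.
- Ages 10 to 18: none in rounds 1 and 2; (646 + 646) / 3,229 = 40.0% in round 3; (452 + 452) / 2,260 = 40.0% in round 4.

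**Inputs for the size of the effect.** From the document: round 1 targets and 85% usable data, so 1,318 × 0.85 ≈ 1,120 people aged 60 and over, and 2 × 1,318 × 0.85 ≈ 2,240 aged 19 to 59. Assumed, because the document gives no figures: a comorbidity in 35% of the older and 10% of the younger group, no association with serostatus within either group, and a 5% two-sided test level. The document states 5% only for the sample size. Three age gradients in seroprevalence are tried, each averaging the planned 10%.

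**Worked case: seroprevalence 14% versus 8%.**
- Seropositive: 1,120 × 0.14 + 2,240 × 0.08 = 156.8 + 179.2 = 336. With the comorbidity: 156.8 × 0.35 + 179.2 × 0.10 = 72.8, or 21.7%.
- Seronegative: 3,360 − 336 = 3,024. With the comorbidity: 963.2 × 0.35 + 2,060.8 × 0.10 = 543.2, or 18.0%.
- Crude odds ratio: (72.8 / 263.2) / (543.2 / 2,480.8) = 1.26. The odds ratio within each age group is 1 by construction.
- Expected test statistic: pooled proportion 616 / 3,360 = 0.1833; standard error √[0.1833 × 0.8167 × (1/336 + 1/3,024)] = 0.02225; z = (0.2167 − 0.1796) / 0.02225 ≈ 1.67.
- Chance of rejection: Φ(1.665 − 1.96) + Φ(−1.665 − 1.96) ≈ 38%.

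**All cases, by simulation (40,000 samples each; crude chi-square against an age-stratified Mantel-Haenszel test).**

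| Seroprevalence, 60+ vs 19–59 | Crude odds ratio | Crude test rejects | Stratified test rejects |
|---|---|---|---|
| 14% vs 8% | 1.26 | 38% | 5% |
| 12% vs 9% | 1.13 | 14% | 5% |
| 11% vs 9.5% | 1.06 | 7.5% (7.0% by the formula above) | 5% |
| 10% vs 10% | 1.00 | 5% | 5% |

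**How much is due to the oversampling.** The same total of 3,360 was used with people aged 60 and over at their natural 6% (201 older, 3,159 younger). The crude odds ratio for 14% versus 8% falls to 1.11, and the crude rejection rates become about 10%, 6% and 5%. The confounding is present without the quotas, and the quotas make it larger.

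**The case against.** The strongest reply is that no conclusion of Phase 1 rests on these tests. Its objective is seroprevalence, its endpoints are proportions, and the sample is sized for ±3% precision. The comparison by serostatus is neither an objective nor an endpoint, and the text promises only description and comparison. Predictors belong to Phase 2, where regression is planned. A crude test also detects a real marginal difference correctly; it misleads only if read as an effect of the factor itself. All of this stands and sets the severity. It does not answer the mismatch: the tests are written down, and in a sample with age quotas even the marginal difference is not that of the population.

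Several stronger readings are tempting and are not supported:

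- A reader might infer that a long list of tests without a multiplicity rule makes false risk factors likely. The document states no significance level for these comparisons and does not call the results risk factors. Any family-wise figure would also need every null to be true, including those for age and for contact with a case. A multiplicity rule or exploratory label is commonly left to an analysis plan or full protocol that is not shown.
- A reader might infer repeated testing, because "A first analysis will be performed after the first collection on day 0". The text does not say that this analysis includes the comparisons by serostatus, nor that they are repeated each round.
- A reader might conclude that age-linked factors would be flagged only because of the quotas. The crude odds ratio of 1.11 at the natural age share shows otherwise.
- Asking for one lead association would impose a hypothesis that Phase 1 does not have.

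**Conclusion.** The point holds as a minor one. The analysis section fixes crude two-group tests for a sample whose age make-up is set by design, and adjusting for strata that are already known is a better method at little cost. Under the assumed 35% and 10% comorbidity prevalence, the crude test rejects in about 38%, 14% or 7% of samples as the seroprevalence gap narrows from 14% versus 8%, through 12% versus 9%, to 11% versus 9.5%. The nominal rate is 5%, and an age-stratified test keeps it.

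The size depends on those assumed prevalences, on the assumed 5% level and on seroprevalence differing by age. With no age gradient there is no excess. The calculation covers the two adult age bands of round 1 only; the entry of ages 10 to 18 at round 3 changes the age mix again and was not simulated. The primary seroprevalence estimate is not affected by this point.

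**What to change.** In the Phase 1 Statistical analysis section, replace or supplement the two-group tests by serological status with a regression of serostatus adjusted for age group, gender and city. Report adjusted odds or prevalence ratios with 95% confidence intervals, and present them as exploratory. Crude descriptive tables can stay. No new data, larger sample or change of significance level is needed. The cost is slightly more analysis work, and fewer factors may be reported as associated with serostatus.
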